## PROTOCOL SYNOPSIS

|                                                                                                                                                                                                                                                                                                                                                                                                                                                                                                                                                           |               |                      |            |                             |          |                              |               |               |          |
|-----------------------------------------------------------------------------------------------------------------------------------------------------------------------------------------------------------------------------------------------------------------------------------------------------------------------------------------------------------------------------------------------------------------------------------------------------------------------------------------------------------------------------------------------------------|---------------|----------------------|------------|-----------------------------|----------|------------------------------|---------------|---------------|----------|
| Protocol Title:
Prospective Clinical Phase II Multibasket Study in Melanoma Patients with advanced Disease                                                                                                                                                                                                                                                                                                                                                                                                                               |               |                      |            |                             |          |                              |               |               |          |
| Sponsor:
University Hospital Essen
[name]
[name]
Represented by [name]. [name]                                                                                                                                                                                                                                                                                                                                                                                                                            |               |                      |            |                             |          |                              |               |               |          |
| Coordinating Investigator:
[name]. [name]
Department of Dermatology, Skin Cancer Center
Comprehensive Cancer Center Essen
[name]
[name],
Germany
[contact]
[contact]
e-mail: [contact]                                                                                                                                                                                                                              |               |                      |            |                             |          |                              |               |               |          |
| Study Design:
This is an open-label, multi-center, single-arm clinical phase II study to further characterize the efficacy and safety of ipilimumab in patients with pretreated, metastatic and/or inoperable melanoma.                                                                                                                                                                                                                                                                                                                         |               |                      |            |                             |          |                              |               |               |          |
| Planned Study Period:

 
 Period of recruiting	8-9 months	
 
 Enrolment start date (FPI):	QII 2011	
 
 Enrolment finish date (LPI):	December 2011	
 
 End of study:	QIV 2012	
 
                                                                                                                                                                                        |               | Period of recruiting | 8-9 months | Enrolment start date (FPI): | QII 2011 | Enrolment finish date (LPI): | December 2011 | End of study: | QIV 2012 |
| Period of recruiting                                                                                                                                                                                                                                                                                                                                                                                                                                                                                                                                      | 8-9 months    |                      |            |                             |          |                              |               |               |          |
| Enrolment start date (FPI):                                                                                                                                                                                                                                                                                                                                                                                                                                                                                                                               | QII 2011      |                      |            |                             |          |                              |               |               |          |
| Enrolment finish date (LPI):                                                                                                                                                                                                                                                                                                                                                                                                                                                                                                                              | December 2011 |                      |            |                             |          |                              |               |               |          |
| End of study:                                                                                                                                                                                                                                                                                                                                                                                                                                                                                                                                             | QIV 2012      |                      |            |                             |          |                              |               |               |          |
| Planned Total Number of Patients:
Up to 200 patients                                                                                                                                                                                                                                                                                                                                                                                                                                                                                            |               |                      |            |                             |          |                              |               |               |          |
| Country(ies) and No. of Sites:
Germany – up to 26 sites                                                                                                                                                                                                                                                                                                                                                                                                                                                                                         |               |                      |            |                             |          |                              |               |               |          |
| Study Rationale
Various phase II clinical studies using ipilimumab in unresectable stage III-IV have been conducted. Results of the first pivotal phase III study MDX010-20 have been presented at ASCO 2010 (O'Day et al., JCO) and are published in NEJM (Hodi et al., NEJM, 2010). In the second ongoing phase III trial CA184-024, a different dose and treatment scheme is currently tested. Results are expected at the end of 2010.
However, due to strictly defined inclusion and exclusion criteria in phase III trials, results of |               |                      |            |                             |          |                              |               |               |          |

registrational trials might not answer all questions regarding safety and efficacy of ipilimumab in all advanced melanoma patient cohorts seen in daily routine. E.g. on one hand, in MDX010-20 trial, only patients positive for HLA-A2 could be enrolled (since patients were randomized in a double-blind fashion in a 1:3:1 ratio to receive HLA-A2-restricted melanoma gp 100 peptide vaccine monotherapy, MDX-010 in combination with melanoma gp100 peptide vaccine, or MDX-010 monotherapy.) In the second currently ongoing phase III study CA184-024 patients were not restricted to HLA-A2+ haplotype. However, another dosing and treatment scheme was tested (combination with DTIC, ipilimumab 10mg/kg and maintenance period following induction phase for patients who benefitted from ipilimumab) for untreated advanced malignant melanoma patients. Patients with primary mucosal melanoma were excluded in CA184-024 study; patients with primary ocular melanoma were excluded in both MDX-010-20 as well as in CA184-024. The currently described study concept with ipilimumab 3mg/kg would make a rational therapeutic strategy in a broad range of pretreated metastatic melanoma patients seen in daily clinical practice.

### **Research Hypothesis**

A large clinical phase II is proposed to treat a broad range of metastatic melanoma patients who have failed at least one systemic treatment in unresectable stage III-IV melanoma in order to further characterize efficacy and safety of ipilimumab in a broad range of clinically relevant patient cohorts seen in daily routine, neither addressed in MDX-010-20 study nor in CA184-024. Enrollment will not be restricted to any specific HLA subtype and patients with uveal or ocular melanoma can be treated with ipilimumab as well. Wide access to ipilimumab in skin cancer-specialized clinical centers will be achieved in addition to a standardized evaluation of its clinical results and a further evaluation of algorithms for the management of side effects. Patients will be treated according to the MDX-010-20 protocol with ipilimumab monotherapy 3mg/kg four times during the induction phase.

### **Treatment:**

Treatment with the anti-CTLA-4 mAb Ipilimumab monotherapy of each patient in the scope of this trial is defined as induction plus re-induction of eligible patients until 12 months after first receipt of study medication

### **Induction phase:**

Ipilimumab will be applied to melanoma patients according to the protocol of the completed Medarex study MDX-010-20: Ipilimumab by IV infusion, 3 mg/kg, day 1 (W1), 22 (W4), 43 (W7), 64 (W10)

### **Re-induction:**

Patients who progress following stable disease of  $\geq 3$  months duration starting from diagnosis at week 12 tumor assessment or patients who have progressed following an initial response (partial or complete) assessed at week 12 may be offered additional cycles of therapy with the originally assigned treatment regimen until off-treatment criteria are met, provided they meet re-treatment eligibility requirements. Please note that re-induction is allowed only if progressive disease was confirmed within not less than 4 weeks. No patient will be re-treated if they experience a Grade 3 or higher gastrointestinal or certain other immune-related adverse events (irAE) (refer to section 5.2 and 5.3). No patient with disease progression following the first cycle of study medication will be permitted to be re-treated with study medication.

**Examinations:**

The disease will be assessed at baseline, at week 12 and for patients with stable disease or better responses, thereafter every 12 weeks in the absence of PD with a maximum of one year after receive of the first treatment. Response evaluation will be done according to immune-related response criteria (Wolchok et al., CCR 2009).

All patients who prematurely discontinued treatment due to a drug-related adverse event prior to Week 12 (in the absence of disease progression) will return for all study visits and procedures including Week 12 and, if appropriate, further re-staging assessments. Any patient with documented progression at any scheduled re-staging visit and who will not receive any re-induction will undergo no further re-staging visits.

**Follow-up phase:**

Survival will be assessed every 3 months after the final dose of Ipilimumab until the end of the follow-up phase for the individual patient. FU phase for each subject is 1 year following first treatment dose. End of study will be at recruitment finished plus 1 year post start of treatment of last patient thus ensuring that 1 year survival rate can be estimated.

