**Study duration:**

End of study is 1 year post LPFV. Therefore expected maximum study duration is 8-9 months (Period of recruiting) accrual + 12 months for follow-up.

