m FU-phase is defined after initial progress and non-eligibility for re-induction. For each subject, survival status (alive/dead and date) will be collected every 3 mths until 1 year post the subjects's first treatment dose.

n Serum and plasma only at screening and at week 12

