## **6. STUDY PROCEDURES AND OBSERVATIONS**

### **6.1. Procedures by Visit**

#### **6.1.1. Study Procedures by Visit and Treatment Cycle**

Note that results of all safety laboratory tests (that is, all chemistry and all hematology results) must be obtained and reviewed before ipilimumab administration, as applicable. All laboratory results must be within the established range before ipilimumab is administered. All induction period laboratory samples must be collected within a window of up to 3 days before administration of ipilimumab. Laboratory evaluations using a local laboratory must be performed and the result examined by the investigator before administration of each dose of ipilimumab.

The disease will be assessed at baseline, after 12 weeks and for patients with stable disease or better responses, thereafter every 12 weeks in the absence of PD to a maximum of one year. Response evaluation will be done according to RECIST and immune-related response criteria (1).

All patients who prematurely discontinue treatment due to a drug-related adverse event prior to Week 12 (in the absence of disease progression) will return for all study visits and procedures including Week 12 and, if appropriate, further re-staging assessments until disease progression is observed.

- Subjects who are no longer receiving ipilimumab because of unacceptable toxicity (refractory Grade  $\geq 3$  irAEs) or due to investigator judgment are followed with tumour assessment until ir PD. Efficacy assessments for these subjects during follow-up are as per the standard of care. Date of death is recorded.
- Subjects who discontinue ipilimumab treatments are followed with tumour assessment until ir PD and should be followed until death or the closure of the study (whichever is first).
- Subjects who are no longer receiving ipilimumab because of progression and who have switched to alternative treatment are not followed formally except to record the date of death.

Any patient with documented progression at any scheduled re-staging visit who is not eligible for re-induction treatment will undergo no further re-staging visits and enters the Follow up phase (FU phase).

At the time of closure of the study (LPFV+12 months), it will be ensured that survival status (alive/dead and date) has been collected for each subject for each subject's full follow-up period (i.e: for 1 year from the subject's first treatment dose).

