**6.1.1.5. FU-Phase**

Patients who have progressed initially and were not eligible for re-induction are followed for survival only on a regular basis e.g. 3 months intervals by phone until death, the trial ends or the patient becomes lost-to-follow-up (LTFU). At the time of closure of the study (LPFV+12 months), it will be ensured that survival status (alive/dead and date) has been collected for each subject for each subject's full follow-up period (i.e: for 1 year from the subject's first treatment dose).

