### **9.1. Sample Size Justification**

Assuming that the entire study cohort will behave as cutaneous melanoma treated with 10mg/kg including maintenance therapy, the 1-year-survival rate will be comparable to the 1-year-survival rate seen in BMS CA184-007,-008, and -022 studies, i.e about 50% (0.5), and the width of the 95% CI will maximally be 14%, corresponding to a lower confidence limit of 0.43 and an upper of 0.57. The 1-year-survival rate in the MDX010-020 study published in NEJM (Hodie et al., 2010) is 43% and the 2-year-survival rate 23% for both ipilimumab arms combined using the 3 mg/kg dosing scheme 4-times over 12 weeks.

The proposed study includes patient subgroups (uveal, mucosal) which we currently have only limited efficacy data for ipilimumab on. Retrospective studies suggest the median survival for mucosal melanoma in Stage IV is around 6 months corresponding - assuming an exponential distribution - to about 13% survival rate at 1 year, and median survival for uveal melanoma is around 11 months corresponding to about 25% survival rate at 1 year (Becker et al., 2002; Penel et al., 2008).

Given the differing median survivals for uveal and mucosal melanoma prior to treatment with ipilimumab, the OS at 1 year will be presented separately for the cohorts, uveal, mucosal and cutaneous melanoma. Assuming 10% (N=20) subjects enrolled have uveal melanoma, and a further 10% have mucosal melanoma, whilst 80% (N=160) of those enrolled have cutaneous melanoma, the width of the 95%CI will, for any survival rate at 1 year, maximally span 41% for the uveal and mucosal cohorts, and 18% for the cutaneous cohort.

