Additional analyses treating survival and PFS as time to event endpoints will be performed i.e.: Kaplan-Meier plots will be produced. These will use the ITT population. Survival will be measured, regardless of any re-induction, from the date of the first on-study ipilimumab dose until date of death. Survival time for subjects, whose date of death is unknown, will be censored at the last date of contact. PFS will be measured, regardless of any re-induction, from the date of the first dose of ipilimumab until the first on-study documented date of progression, as per irRC, or date of death, whichever comes first. PFS time of subjects not known to progress or die, will be censored at the date of the last tumor assessment. Median survival, median PFS, survival rate at 1 year and PFS rate at 6 months, all as derived from the Kaplan-Meier curves, will be presented, together with 95%CI.

Safety will be reported for 70 days (5 half-lives) post last treatment. This period will be considered the on-study safety period. The analysis of safety will be based on the frequency of AEs and their severity for all treated subjects (i.e.: the Safety population). Worst toxicity grades per subject will be tabulated for all AEs. Additionally, drug-related grade 3 or more AEs, immune-related, and serious AEs will be tabulated separately, and listings by subject will be produced for all deaths, all SAEs and all AEs leading to discontinuation of study drug.

All adverse events and serious adverse events recorded during the study will be summarized using descriptive statistics. The incidence of treatment-emergent adverse events (new or worsening from baseline) will be summarized by body system, preferred term, verbatim of adverse event, intensity (based on CTC grades), and relation to the investigational products. Furthermore all adverse events and serious adverse events will be listed.

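### The protocol gives two survival follow-up rules, and under the 12-month rule the supportive median OS often has no upper confidence limit

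*Protocol*

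**What the plan says.** Two places in the Protocol end survival follow-up at 12 months from each patient's own first dose. The synopsis, under Follow-up phase, states "FU phase for each subject is 1 year following first treatment dose". Footnote m of the Time and Events Schedule says that survival status "will be collected every 3 mths until 1 year post the subjects's first treatment dose".

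Two other places set a later end for some patients. Section 6.1.1 says that patients who discontinue ipilimumab "should be followed until death or the closure of the study (whichever is first"). Section 6.1.1.5 has patients who progressed and cannot be re-induced followed "until death, the trial ends or the patient becomes lost-to-follow-up (LTFU"). Both sections then close with a sentence that defines each patient's full follow-up period as 1 year from first dose, so each also disagrees with itself.

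The synopsis, under Study duration, gives the calendar: "expected maximum study duration is 8-9 months (Period of recruiting) accrual + 12 months for follow-up". That is 20-21 months.

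Section 9.5 plans these estimates with 95% CIs: "Median survival, median PFS, survival rate at 1 year and PFS rate at 6 months, all as derived from the Kaplan-Meier curves". Survival is censored at last contact, and the section sets no administrative cut at month 12.

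**The concern.** The follow-up rule decides what sites collect, so it cannot be settled at analysis. For the first patients enrolled, the two rules differ by up to 8-9 months. If sites read them differently, follow-up after month 12 will depend on site habit, or on whether a patient stopped treatment or progressed. Kaplan-Meier censoring after month 12 could then be informative.

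If everyone stops at month 12, the second problem is precision. The planning assumptions put between 43% and 50% of patients alive at that point. The survival curve then ends only a little below one half, or at it. The upper confidence limit of a median is the time at which the upper confidence band of the curve falls through one half, and the curve may end before that happens. Meanwhile patients enrolled early are still alive in an open trial and no longer contribute.

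**Working it through.** 1. **Inputs.**
   - N = 200 (synopsis).
   - One-year survival of 45.6%, rounded to 0.5, and median 10.1 months (synopsis, Sample Size Justification).
   - One-year survival of about 50%, and 43% at one year with 23% at two years for the combined 3 mg/kg arms of the pivotal trial (section 9.1).
   - Cohort shares 80/10/10, with historical one-year rates of 25% uveal and 13% mucosal (section 9.1).
   - Accrual 8-9 months, taken as uniform (an assumption).

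2. **The plan's own figure.** Section 9.1 has "i.e about 50% (0.5), and the width of the 95% CI will maximally be 14" per cent, with limits 0.43 and 0.57. The exact Clopper-Pearson interval at 100/200 is 0.429 to 0.571, width 14.3%. The Wald width is 13.9%. The stated figure reproduces.

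3. **When the upper limit exists.** With complete follow-up to month 12 and none after, the upper pointwise 95% limit of S(t) must fall below 0.5 by month 12.
   - 86 alive: S = 0.430, SE = √(0.43 × 0.57/200) = 0.0350, upper limit 0.430 + 1.96 × 0.0350 = 0.499. It exists.
   - 87 alive: S = 0.435, SE = 0.0351, upper limit 0.504. It does not exist.
   - The log-log interval gives the same boundary (0.497 and 0.502).

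4. **Other rates to test.** An exponential with median 10.1 months gives 0.5^(12/10.1) = 43.9% at month 12. The cohort mix at the historical rates gives 0.8 × 45.6 + 0.1 × 25 + 0.1 × 13 = 40.3%.

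5. **Probabilities under the 12-month cut.** With X ~ Binomial(200, S(12)), there is no upper limit if X > 86, and the median is not reached if X > 100.

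| One-year survival | No upper limit | Median not reached |
|---|---|---|
| 50% | 97% | 47% |
| 45.6% | 75% | 9% |
| 43.9% | 57% | 4% |
| 43% | 47% | 2% |
| 40.3% | 20% | 0.2% |

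   Kaplan-Meier simulation with log-log limits (4,000 trials per setting) agrees, with 97%, 74-75% and 45-47% lacking an upper limit at 50%, 45.6% and 43%. An assumed 5% loss by month 12 changes little. For the cutaneous cohort (N = 160) the upper limit is missing in 76-81% of trials at 45.6% and about 97% at 50%, depending on the interval type.

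6. **Everyone followed to closure.** Each patient has 12 months plus a uniform 0 to 8-9 months.
   - 43% at one year, 23% at two: at most 0.2% lack an upper limit.
   - 45.6% at one year, 23% at two: at most about 0.3%.
   - 50% at one year, exponential tail (25% at two): about 1-2%.
   - 50% at one year, assumed flatter tail (30% at two): 7-12%.

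**The case against.** The 12-month cut looks deliberate. The synopsis and section 3.5 tie it to estimating one-year survival, which is the primary endpoint and is fully served. A reader might infer that a secondary endpoint cannot be delivered. The documents do not support that. The synopsis lists overall survival, not its median. Section 9.5 places the median among additional analyses and calls everything beyond the primary exploratory. The curve and the one-year rate with its CI are still produced. The protocol itself reports open-ended intervals for median OS, in Table 4 and section 1.3.6. This stands, and makes the median a supportive estimate.

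A reader might also infer that the median is expected almost exactly at the cut. That fits only the 50% rate. In section 9.1 this rate comes from 10 mg/kg with maintenance, and in the synopsis it is a rounding of 45.6%. The stated median of 10.1 months lies about two months before the cut, and 43% is the pivotal trial's rate at 3 mg/kg. This also stands: the failure rate is a range, and at 43% it is close to a coin toss.

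The contradiction can be read narrowly. Sections 1.2 and 5.2 use an individual end of trial, or patient study period, of 12 months from first dose, so trial end in section 6.1.1.5 might mean that. The reading does not fit the study-closure wording in section 6.1.1. It shows why the wording must be settled, and also that the cut cannot be taken as the only rule in force.

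Finally, the rationale cites two-year survival, so longer follow-up might seem to supply it. It would not: closure comes at 20-21 months and no patient reaches 24.

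**Conclusion.** The point holds in limited form. The four follow-up statements conflict and must be reconciled. If the 12-month rule governs, the supportive median OS lacks an upper limit in about 75% of trials at 45.6%, 97% at 50%, 47% at 43% and 20% at about 40%. The median itself is missed in about 9%, 47%, 2% and under 1%. The primary 12-month rate is untouched.

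The figures assume 200 treated patients and essentially complete follow-up to month 12. The gain from following to closure further assumes uniform accrual and a tail after month 12. The tail matters mainly at 50%, where the residual failure is about 1% to 12%. A flatter tail is plausible: Table 4 shows 47.22% at one year and 32.83% at two for one study, against 0.4722² = 22.3% under an exponential. The 40% scenario uses the protocol's historical uveal and mucosal rates. These do not match its quoted medians under an exponential (11 months gives 47%, 6 months gives 25%). With the matching rates the mix is 43.7% and the upper limit is missing in 55% of trials.

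This is a cheap improvement worth making. It is not a flaw in the primary analysis.

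**What to change.** State one rule in the synopsis (Follow-up phase), footnote m, section 6.1.1 and section 6.1.1.5: survival status every 3 months until death, loss to follow-up or study closure, with at least 12 months from first dose for every patient. Keep the 12-month survival rate as the primary endpoint. In section 9.5, say that Kaplan-Meier OS uses all follow-up to closure. Sample size and closure date do not change.

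The cost is a protocol amendment with ethics review under section 12.2, with revised consent if the change is judged substantial, plus telephone contacts. At 45.6% about 200 × 0.456 = 91 patients are alive at month 12. Mean extra follow-up is 8.5/2 = 4.25 months, or 4.25/3 = 1.4 calls each, so roughly 130 calls in total, and fewer once deaths after month 12 are allowed for.

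If the sponsor prefers to keep the 12-month cut, sections 6.1.1 and 6.1.1.5 should be brought into line with it, and section 9.5 should say that the interval for median survival may have no upper limit.
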